## Abstract

**Background:** Autism Spectrum Disorder (ASD or autism) is characterized by difficulties in social communication and interaction, which negatively impact on individuals and their families' quality of life. Currently no pharmacological interventions have been shown to be effective for improving social communication in autism. Previous trials have indicated the potential of arbaclofen for improving social function among autistic children and adolescents with fluent speech. The AIMS2TRIALS-Clinical Trial 1 (AIMS-CT1) will examine whether arbaclofen is superior to placebo in improving social function and other secondary outcomes over 16 weeks, along with safety and tolerability profiles.

**Methods:** AIMS-CT1 is an international, multi-site, double-blind, parallel group Phase II randomized clinical trial. It will include 130 males and females aged 5:0–17:11 years, with a diagnosis of ASD and fluent speech. Eligible participants will be randomized on a ratio of 1:1 for a 16-week treatment period. Medication will be titrated over 5 weeks. The primary outcome is the effect on social function from weeks 0 to 16 measured on the Socialization domain of the Vineland Adaptive Behavior Scales, 3rd edition^TM^. Secondary outcome measures include the CGI–S (Clinical Global Impression–Severity), CGI–I (Clinical Global Impression–Improvement), other areas of adaptive function, social communication and other autism symptoms, co-occurring behavior problems and health-related quality of life. Genetic and electrophysiological markers will be examined as potential stratifiers for treatment response. Exploratory novel digital technologies will also be used to measure change, examining simultaneously the validity of digital biomarkers in natural environments. The safety and tolerability of the drug will also be examined. Our protocol is very closely aligned with a parallel Canadian trial of 90 participants (ARBA Study, US NCT number: NCT03887676) to allow for secondary combined analyses. Outcomes will be compared using both an Intent-to-reat and Per Protocol approach.

**Discussion:** The outcomes of this trial, combined with the parallel Canadian trial, will contribute to the evidence base for medications used to help social difficulties among young autistic individuals; demonstrate the capabilities of the AIMS-2-TRIALS network of academic centers to deliver clinical trials; and support future drug development.

**Clinical Trial Registration:** EudraCT number: 2018-000942-21 and ClinicalTrials.gov registry number: NCT03682978. Currently under protocol v.7.2, dated 20.11.2020.

## Background

Autism Spectrum Disorder (ASD or autism) is a highly heritable disorder with prevalence rates in childhood between 1 and 2% (1, 2). Clinical presentation of autistic symptoms typically becomes apparent in early childhood and includes impairments in social interaction and communication, and the presence of sensory anomalies and repetitive and stereotyped behaviors [DSM-5; (3)]. Clinical presentation is highly heterogeneous, depending mainly on age, language, global cognitive levels and accompanying behavioral and/or emotional difficulties (4). A coherent understanding of the neurobiology of autism has not yet been achieved (5). However, recent findings suggest that autism results, in most cases, from atypical neurodevelopmental processes that have their onset *in utero*, and on-going physiopathological mechanisms at molecular, cellular, and circuit levels (6).

The heterogeneity of ASD is not only great at the level of the clinical phenotype but also at the level of the underlying neurobiological mechanisms that may lead to diverse phenotypes. Therefore, different molecules will likely improve deviant behaviors in different subgroups of patients. The study of pathogenic *de novo* mutations in large consortia has led to the identification of several different biological mechanisms as particularly relevant in the etiology of ASD. The study of differential neuropathological pathways that lead to distinct phenotypes and the possibility of finding biomarkers that may index differential pathways or disease trajectories within ASD is one of the most prominent topics in the study of the etiology of ASD and one included in the main objectives of the AIMS-2 TRIALS network (https://www.aims-2-trials.eu/). AIMS-2-TRIALS (Autism Innovative Medicine Studies-2-Trials) began in June 2018 and will run until May 2023. Its purpose is to accelerate medicine development, in particular, precision medicine, via a network of connected scientists and stakeholders across Europe and beyond. The research programme includes a range of work packages and sub-studies led by different academic, scientific and industry professionals to explore how autism develops, from before birth to adulthood, and how this varies in this population. The main aim of the consortium is to study biological markers and relate them to specific phenotypes, which could ultimately benefit from tailored treatments. The consortium will test, in specific subpopulations, new and repurposed medicines to help with social difficulties, repetitive behaviors and sensory processing. Currently, evidence-supported treatment options for core symptoms of autism do not include any pharmacological intervention. The clinical and biological heterogeneity of ASD may partially underlie the lack of positive results in clinical trials. Attention has turned recently to mechanistically targeted treatments. Among the most evidence-supported mechanisms is an excitatory-inhibitory unbalance that affects in, as yet unknown way, the proper coordination of the GABA and glutamate action at the appropriate developmental stages (7).

Glutamate is the most prevalent excitatory neurotransmitter, while gamma-aminobutyric acid (GABA) is the most prevalent inhibitory neurotransmitter in the human brain. Disruptions in GABA-ergic or glutamate signaling have been associated also with other neurodevelopmental disorders including autism and Fragile X Syndrome (FXS), as well as epilepsy (8, 9). A disruption in the excitatory/inhibitory (E-I) ratio is proposed to characterize the autistic brain (9, 10), but the direction of any such imbalance is less clear (11). Dysfunction in GABA signaling has been related to autism-like stereotypies (12). Arbaclofen has been tested in three moderately-sized studies: one in autism, and two in fragile X syndrome. New biomarker investigations have shown that arbaclofen modulates binocular rivalry, which was previously found to be abnormal in autism (13). In healthy controls, they found that arbaclofen increased perceptual suppression relative to placebo, consistent with the understanding of excitatory:inhibitory dynamics in the visual circuits for binocular rivalry. McAlonan et al. (14) very recently reported that arbaclofen dose-dependently rescues differences in visual contrast perception in adults with autism. These psychophysical effects were accompanied by changes in functional connectivity in multiple cortical circuits.

Taking all this evidence together it seems promising to explore medications that target E-I imbalance. Indeed, previous studies with GABA modulators have shown the potential for improving core autistic symptoms. For example, a recent study from the EU-AIMS consortium reported that differences in E-I balance can be 'shifted' using a GABA acting drug (riluzole), and that abnormalities in functional connectivity can be “normalized” by targeting E-I, including autistic adults (15).

One particularly fruitful target may be GABA type B receptors (GABAB). GABAB are crucial for maintaining the E-I balance and pervasive defects in GABAB receptor expression and activity have been associated with autism and are postulated to contribute to co-morbid seizure activity and cognitive impairment (8).

Arbaclofen (previously known as STX209) is a selective GABAB receptor agonist that augments GABA-ergic activity, inhibits presynaptic release of glutamate, inhibits postsynaptic transmission, and modulates intracellular signaling (16–18). Arbaclofen is the active enantiomer of racemic baclofen, an EMA and FDA approved GABAB agonist for spasticity. Baclofen has demonstrated efficacy in treating hyperactivity and audiogenic seizure phenotypes in the fragile X knockout mouse (19, 20). FXS mice models have been found to exhibit deficient GABA-mediated inhibitory neurotransmission particularly notable in the amygdala (21) brain region associated with affective behaviors involving emotional understanding and social interaction. Through elevation of GABA-ergic inhibitory activity, arbaclofen might alleviate autistic symptoms associated with social anxiety and emotional hyperarousal.

A previous trial has investigated whether Arbaclofen improves social difficulties in autism. Seaside Therapeutics initially conducted an open-label, flexible-dose, 8-week Phase II trial of arbaclofen in 32 autistic children and adolescents. Participants were treated with up to 10 mg thrice a day of arbaclofen and reported broad beneficial effects on autistic symptoms with no significant safety or tolerability concerns (22). This study was followed by a randomized, double-blind, placebo-controlled Phase II trial of arbaclofen in 150 autistic individuals between 5 and 21 years of age (23). Following the 12 weeks treatment, participants on arbaclofen and placebo showed no difference on the primary outcome measure [Social Withdrawal/Lethargy subscale of the Aberrant Behavior Checklist; (24)], but showed a nominally significant advantage on the Clinical Global Impression – Severity (CGI–S; 24, 25) for the arbaclofen group. *Post-hoc* exploration showed that drug-related improvements tended to be greater among the more verbally fluent individuals; and per-protocol analysis revealed a nominally significant improvement in of the Socialization domain of the Vineland Adaptive Behavior Scales, 2nd edition [VABS−2; (25)] and when scored by the same clinician both pre- and post-intervention, as per protocol. Safety results showed generally good tolerability, with somnolence and affect lability being more frequent in the active arm of the study. Given the results shown, and in view of the high heterogeneity of the condition that may be masking overall group results, there is rationale to investigate whether more specific, targeted and homogeneous groups (i.e., verbally fluent individuals) may benefit from the treatment with arbaclofen. Therefore, even though with the evidence available so far it is impossible to disentangle whether the positive results on verbally fluent children, adolescents and adults are due to the age and/or language level of the individuals in this group or whether it is the appropriateness of the assessment instruments used, we built on secondary outcome analyses from the Seaside study, and a homogeneous group of verbally fluent individuals was the target of the current clinical trial.

## Objectives

The primary objective of AIMS-CT1 is to examine the effect of arbaclofen vs. placebo on social function and behavior, as assessed through the Socialization Domain of the Vineland Adaptive Behavior Scales, 3rd edition [VABS−3; (26)]. We hypothesize that arbaclofen will be superior in improving social function impairments when compared to placebo. The key secondary objective is to examine the effect of arbaclofen vs. placebo on global functioning, as measured by CGI-I. Other secondary objectives are to examine the effects on other areas of adaptive function (communication and daily living skills), social communication behavior and other autistic symptoms, co-occurring behavior problems and health-related quality of life. The safety and tolerability of arbaclofen vs. placebo will also be examined. An exploratory objective is to examine whether electrophysiology and sensory discrimination is associated with treatment response to obtain pilot evidence for a predictive biomarker for future trials. An optional DNA sample (with an specific informed consent form) may help us to identify possible response genetic markers. Furthermore, this study adds the use of a novel, exploratory digital biomarker component that will collect data in naturalistic settings with minimal burden for the families. The use of digital biomarkers aims to gather more objective measures of social interaction and understanding than caregivers- or self- reports. They consist of active tasks (social games on a smartphone), passive monitoring of daily behaviors and surveys to participants and caregivers.

## Methods

### Trial Design

The AIMS-CT1 is an international, multi-site, double-blind, parallel group randomized placebo-controlled Phase II trial. An Autism Representatives Group created in collaboration with Autistica's DISCOVER Research Network participated in several meetings along the trial and read and gave advice and opinion to the relevant final documents before these were submitted to the Regulatory Agencies. The study will examine the superiority of arbaclofen vs. placebo on the primary and secondary outcomes, along with safety and tolerability profiles over 16 weeks. Participants (*N* = 130) will be allocated to arbaclofen or placebo on a ratio of 1:1 and recruited across seven academic sites in Spain, UK and France. The trial design represents a refinement of the previous study of arbaclofen in ASD (23) and is summarized in Figure 1. In collaboration with the Province of Ontario Neurodevelopmental Disorders Network (POND) our protocol is very closely aligned with a parallel Canadian trial of 90 participants (ARBA Study: NCT03887676) for subsequent combination of data.

**Figure 1 F1:**
[figure not shown]
CONSORT diagram showing trial and participant flow through the trial (based on CONSORT guidelines).

### Participants

#### Inclusion Criteria

Male and female participants aged between 5:0 and 17:11 years at time of consent, with a diagnosis of ASD according to the DSM-5 (3) criteria and complex verbal language [defined as qualifying for an Autism Diagnostic Observation Schedule−2 (ADOS−2) Module 3 or 4 assessment (27), as determined by a clinically-certified ADOS-2 rater supervised by the local research-reliable ADOS-2 lead (see Requirements in Additional Material 5)].The parent/carer (hereafter parent; for brevity) can speak and understand the local language.The participant resides with the parent who will complete the primary outcome.Willingness to comply with the medication and research protocols.Pharmacological treatment affecting behavior stable for at least 6 weeks prior to screening, with no planned changes for the duration of the trial.Psychotherapeutic/psychosocial interventions affecting behavior stable for at least 3 months prior to screening, with no planned changes for the duration of the trial.Seizure history stable with anticonvulsant medication and seizure free for at least 6 months prior to screening. If anticonvulsant medication has not been stable for at least 3 months, the participant must be seizure free for at least 3 years prior to screening.Negative pregnancy test for female participants of childbearing potential.Female participants, and female partners of male participants, who are of childbearing potential and sexually active must agree to use highly effective forms of contraception.Participant able to take medication orally.

#### Exclusion Criteria

Any medical condition that may interfere with the conduct of the trial, confound interpretation or endanger the participant's well-being. This includes but is not limited to impairment of renal function, evidence or history of malignancy, any significant hematological, endocrine, respiratory, hepatic, cardiovascular or gastrointestinal disease, or any clinically significant abnormalities on the electrocardiogram (ECG).Prohibited concomitant medications are those that include GABA agonists or modulators [e.g., vigabatrin, tiagapine, clobazam, regular benzodiazepine use (prn and hs use allowed), riluzole].Participants who have taken another investigational medicinal product in the 30 days prior to screening or have been involved in a previous trial of arbaclofen.A history of hypersensitivity to racemic baclofen.Rare hereditary problems of galactose intolerance, the lactase deficiency or glucose-galactose malabsorption.Porphyria.Active peptic ulceration.Engagement in illicit substance or alcohol abuse, according to DSM-5 criteria.Breastfeeding females.

Written informed consent will be signed by the participant's parent/carer/legal guardian. The participant will sign the informed consent form or assent form, following local laws and regulations.

### Interventions

Arbaclofen manufactured for this trial comes as round white orally disintegrating strawberry-flavored tablets with beveled edges, in strengths of 5, 10, 15, and 20 mg. It is stored at room temperature and will be packed in a box in blister cards of seven tablets. A flexible dose titration schedule will be utilized during the first 5 weeks of treatment (see Table 1). Dosing will be stratified by age. For participants aged 5–11 years at time of consent, the starting dose will be 5 mg once daily and increased to a maximum of 15 mg three times a day. For participants aged 12–17 years at consent, the starting dose will be 5 mg twice a day and increased to a maximum of 20 mg three times a day. Dosing titration is similar to Veenstra-VanderWeele et al. (23) with the addition of one higher dose to be tested in adolescents. If a participant does not tolerate a dose increase, under clinicians' advice, he or she should return to the previous dose level and remain at that level for the remainder of treatment. No change will be made to dosing after the 5-week titration period, unless for safety reasons. The treatment period of 16 weeks is 33% longer than in the study of Veenstra-VanderWeele et al. (23), in which the numerical difference between arbaclofen and placebo groups on the CGI-S had not plateaued at 12 weeks. At the end of treatment, the study medication will be tapered down over a period of up to 13 days.

**Table 1 T1:** Dosing and tapering down regime for arbaclofen stratified by age.

**Timepoint**	**Age of participant**			
	**5–11 years**		**12–17 years**	
	**Strength**	**Frequency of administration**	**Strength**	**Frequency of administration**
Week 1 (Day 1, V1)	5 mg	Once daily	5 mg	Twice daily
Week 2 (Day 8)	5 mg	Twice daily	10 mg	Twice daily
Week 3 (Day 15, V2)	10 mg	Twice daily	10 mg	Three times a day
Week 4 (Day 22)	10 mg	Three times a day	15 mg	Three times a day
Weeks 5–16 (Day 29+, V3)	15 mg	Three times a day	20 mg	Three times a day
**Tapering down regime for those on maximum dose at week 16, V7**				
Days 113–116, (V7+3 days)	10 mg	Three times a day	15 mg	Three times a day
Day 117–119	10 mg	Twice daily	10 mg	Three times a day
Day 120–122	5 mg	Twice daily	10 mg	Twice daily
Day 123–125	5 mg	Once daily	5 mg	Twice daily
Day 126	None	–	None	–

*V, Visit*.

The comparator is a placebo tablet. The placebo tablets will have a similar shape, mass, color, smell and taste to the arbaclofen tablets and be provided in identical blister cards of seven tablets in an identical box. The placebo tablets will be administered at the same frequency as described above for arbaclofen and stratified by age. The packs will be released to a blinded study team member for dispensing.

### Randomization and Allocation

Randomization of participants will be performed 1:1 into arbaclofen vs. placebo by a randomization website (Interactive Web Response System—IWRS) developed by the Data Management Department of the Julius Center, University Medical Center Utrecht (UMCU). Allocation will be sent to an unblinded dedicated pharmacist at each individual site as specified in a separate Pharmacy Manual. A central unblinded monitor will double check dispensation regularly. The rest of the study members are blind to allocation. Randomization will be stratified by site and age group (5–11 years old; 12–17 years old). Unblinding will only happen if the information can help treat an adverse event and for safety reasons.

### Outcomes

Table 2 describes all outcomes, safety and sample characterization measures used in the trial. Following *post-hoc* findings in Veenstra-VanderWeele et al. (23), the primary outcome measure chosen is social function as measured by the Vineland Adaptive Behavior Scales, Third Edition (VABS-3)– socialization domain (26) administered by the same rater along the trial, preferably blinded to other outcome measures within a given patient.

**Table 2 T2:** List of study measures.

**Name of measure**	**Measure details**
**Primary outcome**	
Socialization domain of the Vineland Adaptive Behavior Scales, 3rd edition (VABS−3) (26)	The Socialization Domain of the VABS−3 measures social function and behavior, covering interpersonal relationships, play and leisure and coping skills. The informant (parent/carer) is required to reside with the participant. The same informant and interviewer will be used at both timepoints, and any change will be reported as a protocol deviation, and wherever possible the interviewer will be blind to other study assessments. Interviewers administering the VABS−3 will be required to achieve 90% reliability with a gold standard rater in order to administer it for the trial. Regular reliability meetings will be scheduled for VABS−3 gold standard raters and interviewers across study sites to maintain reliability.
**Key secondary outcomes**	
Clinical Global Impression – Severity (CGI–S) scale (28, 29)	The CGI–S will assess the severity of impairment in global functioning, including but not limited to social engagement, internalizing and externalizing problems. It is rated on a 7-point scale ranging from 1 (normal, not at all impaired) to 7 (among the most extremely impaired) by a treating clinician. A CGI-S score of 3 (mildly impaired) will be the anchor applied to all participants meeting diagnostic criteria for ASD, with higher scores indicating significant co-occurring problems.
Clinical Global Impression – Improvement (CGI–I) scale (28, 29)	The Clinical Global Impression – Improvement (CGI–I) scale will measure improvement in global functioning during the previous week since treatment initiation. It will be rated by a treating clinician on a 7-point scale ranging from 1 (very much improved) to 7 (very much worse), with 4 representing no change. All available information will be used to inform clinical judgement. The CGI–I scores will also be used to assess safety, with participants who have CGI–I scores of 6 or more (much or very much worse) for two or more consecutive visits being discontinued from the trial.

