### Statistical Analysis

Analysis will be performed both with an Intent to Treat (ITT) and as Per Protocol (PP) approach. The initial efficacy analysis will use the ITT sample, which includes all participants randomized who have at least one dose of medication and one post-baseline assessment. To be included in the PP sample, participants will fulfill ITT criteria and have attended at least 80% of the visits, have taken at least 70% of the prescribed medication and have a consistent pre- and post-intervention VABS−3 clinician rater.

Efficacy will be indicated by a difference between treatment arms at week 16, using Analysis of Covariance (ANCOVA; with follow-up score used as the dependent variable and treatment group as a factor) or logistic regression, and Chi-Square techniques, as appropriate. Age will be adjusted for and baseline scores will be used as covariates. Hypothesis testing will be performed at the 5% level of significance for 2-sided tests. Safety analyses will be conducted on all participants taking at least one dose of study medication by calculating the incidence of adverse events in each arm and summarizing laboratory and ECG assessments, physical examinations and vital signs.

A secondary analysis will be conducted by combining data from AIMS-CT1 and the ARBA Study to ensure statistical power for the assessment of efficacy of the primary outcome variable. Additional analyses will consider variables or sub-variables that will be different from or derivative of the primary and secondary hypotheses. Another level of analysis will look at data of individual sites. Power calculation was made for the primary outcome (VABS-3 social function domain), which justifies the a priori planned combination of the data of this study with that of ARBA Study in Canada. Other results will be considered secondary results and therefore more exploratory and hypotheses-generating.

While no interim analysis is planned, if necessary, the Data Monitoring Committee (DMC) will consider it and inform the Sponsor whether premature termination criteria are met.

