### Adverse Event Reporting

A medical history and physical examination will be conducted at screening to assist with interpretation of any adverse events (AEs), whether serious (SAEs) or non-serious, that occur during participation in the trial. The standard definition of AEs and SAEs will apply. In addition, pregnancy (in participant, or female partners of male participants), overdose (either accidental or intentional), cancer, potential drug-induced liver injury and suspected transmission of an infectious agent will be recorded as SAEs and follow these reporting regulations. In all cases of pregnancy, the treatment will be permanently discontinued in an appropriate manner and follow-up information on the course of pregnancy should be recorded if permission is given by the participant.

AEs and SAEs may be reported by the participant and/or their parent or found through medical examination or laboratory testing during phone call monitoring or face-to-face visits. The nature of each event, onset, duration and severity will be established and recorded, regardless of whether the event is related to the study treatment or not. AEs will be recorded from the initiation of study treatment until the final visit. All SAEs that occur between screening and up until 30 days of the last dose of the study treatment will be recorded. All AEs and SAEs will be followed-up proactively at subsequent visits/phone calls until either resolution, the condition stabilizes, the event is otherwise explained, or the participant is lost to follow-up. Follow-up is also required for AEs that cause interruption or discontinuation of the study treatment.

Usual convention will be used for reporting all AEs and SAEs following local laws and regulations. All SAEs will be reported to the sponsor and sponsor delegate within 24 h of the study site becoming aware of the event. Any Suspected, Unexpected Serious Adverse Reactions (SUSARs) will be reported to the appropriate regulatory authorities following local and global guidelines and requirements.

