#### COVID Pandemic Adjustments

In March 2020, the WHO declared a COVID-19 global pandemic that would eventually affect health systems all over the globe. The European Medicines Agency (EMA) and the National Regulation Authorities, working with all relevant stakeholders, acknowledged the impact of the pandemic on the conduct of clinical trials and have been issuing additional guidelines for their management. The Sponsor and Principal Investigators of the present clinical trial have taken into account all relevant guidelines and local legislations and have made and reported to the authorities for their approval the appropriate adjustments to the design and conduct of the study. All these adjustments have been included in the updated versions of the Protocol. The most significant ones are: (i) recruitment of new participants was halted during the period that National global lockdowns were in place, (ii) some physical visits were converted into remote visits at the beginning of the pandemic; by phone and/or video-conferencing depending on the assessment instrument after authors/supervisors of the main evaluation instruments were consulted; in this case, vital signs were recorded at local pharmacies; primary outcome measure (social function by the VABS-3 social domain score) was conducted via videoconference at the time of lockdown or whenever it was more risky for the families to attend the hospital, by the same rater and with the same informant; the same format (video or in-site) was maintained for visit 1 and visit 7 for the same patient (iii) transferring of participants specific assessments (e.g., EEG) to investigational facilities away from risk zones or, if possible, to the participants' homes, (iv) transfer of sample extraction, medication provision (ensuring maintenance of temperature control) and other medical/nursing procedures to authorized local facilities and/or participants' homes if possible, (v) on-site monitoring transferred to hired local monitors (vi) local instructions followed at all times for screening for COVID-19 symptoms and enhanced social distancing and protection and cleaning regimes are in place as per site local instructions. For all decisions, a benefit-risk balance of the integrity of the trial and well-being of the participants was taken into consideration with safety always being the prevailing concern.

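### As worded, the CGI-I safety rule removes participants from the trial rather than from study drug, so those who trigger it before visit 7 have no week-16 VABS-3 score

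*Protocol article*

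**What the plan says.** The rule stands in the CGI-I entry of Table 2 (Key secondary outcomes): participants with CGI-I "scores of 6 or more (much or very much worse) for two or more consecutive visits being discontinued from the trial". What ends is trial participation, not medication.

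The other parts of the article that bear on it are:

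- **Primary outcome timing.** Table 2 gives VABS-3 two timepoints: "The same informant and interviewer will be used at both timepoints". COVID Pandemic Adjustments identifies them: "the same format (video or in-site) was maintained for visit 1 and visit 7 for the same patient". Table 1 places visit 7 at week 16.
- **Analysis.** Statistical Analysis states "Efficacy will be indicated by a difference between treatment arms at week 16", using ANCOVA on the follow-up score. The ITT sample "includes all participants randomized who have at least one dose of medication and one post-baseline assessment".
- **Follow-up after stopping.** Adverse Event Reporting says "Follow-up is also required for AEs that cause interruption or discontinuation of the study treatment". The article describes no efficacy assessment after stopping.

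**The concern.** A safety rule needs to stop exposure. It does not need to stop observation. As worded, this rule does both, and it acts on participants whom a clinician has twice rated much or very much worse. Their week-16 Socialization score is then missing because of something that happened after randomisation, possibly because of treatment.

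The week-16 comparison would be biased if the arms differ in how many exit, or in how those who exit would have scored. The direction cannot be predicted. CGI-I is a global rating, so a participant who exits need not do worse on Socialization. CGI-I also measures the key secondary objective, so the rule selects directly on that endpoint and loses its week-16 value as well.

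The choice of missing-data method can be left to the analysis plan. Whether the visit takes place cannot, because it is settled during trial conduct.

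**Working it through.** **Does the wording lead to the loss?**

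1. The rule needs two consecutive CGI-I ratings of 6 or more. Triggering it on treatment therefore requires at least two post-baseline ratings.
2. Such a participant has taken drug and has a post-baseline assessment. The ITT definition is met, since it does not require that assessment to be a VABS-3.
3. VABS-3 has no timepoint between visit 1 and visit 7. A participant removed before visit 7 has no follow-up Socialization score for the ANCOVA.
4. If the second rating of 6 or more first occurs at visit 7, nothing is lost.
5. Adverse Event Reporting refers to discontinuing the study treatment, so the article does use that separate term. The literal reading of Table 2 is a fair one.

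**How large could the bias be?** The plan gives no figure for this rule: no exit rate and no outcome for those who exit. Only the scale comes from Sample Size: a target difference of 5.3, SD 15, and 130 participants allocated 1:1, so 65 per arm. (The stated 100 per arm does not reproduce from those inputs with a two-sided 5% test and 80% power, which gives 126; a one-sided 5% test gives 100. Nothing below depends on it.)

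Let e be the proportion of an arm that exits before visit 7, and d the amount by which those participants would score below the rest at week 16. If the rest average m, the full-arm mean is m − e·d and the observed mean is m. Each arm is overstated by e·d, so

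bias of the difference = e_A·d_A − e_P·d_P (A arbaclofen, P placebo).

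All e and d below are assumed. A positive shift favours arbaclofen.

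| e_A | e_P | d_A | d_P | Shift (points) | Share of 5.3 |
|---|---|---|---|---|---|
| 5% | 2% | 10 | 10 | 0.50 − 0.20 = 0.30 | 5.7% |
| 2% | 5% | 10 | 10 | 0.20 − 0.50 = −0.30 | −5.7% |
| 5% | 5% | 10 | 5 | 0.50 − 0.25 = 0.25 | 4.7% |
| 5% | 2% | 5 | 5 | 0.25 − 0.10 = 0.15 | 2.8% |
| 5% | 2% | 15 | 15 | 0.75 − 0.30 = 0.45 | 8.5% |
| 5% | 5% | 10 | 10 | 0 | 0 |
| any | any | 0 | 0 | 0 | 0 |

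**What would the fix recover?** Suppose half of those who exit attend visit 7 and are typical of them. The remaining bias per arm is e·d·(1 − 0.5/(1 − e/2)):

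- arbaclofen: 0.50 × (1 − 0.5/0.975) = 0.244
- placebo: 0.20 × (1 − 0.5/0.99) = 0.099
- difference: 0.14, down from 0.30.

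**How many participants?** At 5% vs 2%: 0.05 × 65 = 3.25 and 0.02 × 65 = 1.3, together 4.55, about 5. At 5% in both arms: 6.5, about 7.

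**Power.** For 130 participants, SD 15, a two-sided test and 10% other attrition, power is 48.0% with no exits and 46.1% with 5% exits. The loss of power is minor; the concern is bias.

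**The case against.** The case against rests on five points.

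- **The source is a summary.** The rule is one phrase in a table cell describing an instrument. Withdrawal procedures normally sit in the full protocol, and neither that nor Table 3 nor Figure 1 is shown. The phrase may be shorthand for stopping medication, and continued adverse-event follow-up suggests contact is kept. This stands as a limit: the finding concerns the rule as the article words it. But adverse-event follow-up is not a VABS-3 interview, and an early-termination VABS-3 would not be a week-16 score.
- **Missing data belong to the analysis plan, and 10% attrition is already allowed for.** The method does belong there. No method restores a score that was never collected, and an attrition allowance covers numbers, not bias.
- **The effect is small and assumed.** This stands. With 65 per arm the standard error of an unadjusted difference is 15 × √(2/65) = 2.6 points, so 0.3 is about 0.11 of a standard error.
- **Recovered scores would be off drug.** If the worsening was drug-related and reversible, the week-16 deficit could be near zero, and so could the bias. Using such scores is an estimand choice. Both points are right, but analysing participants in their assigned arm whether or not they stayed on drug fits the plan's own ITT approach.
- **The amendment is not free.** It needs approval in three countries, and a change in this trial alone could make the pooled analysis with the Canadian trial inconsistent. This stands and belongs in the cost.

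**Conclusion.** The concern holds for the article's wording. Followed literally, the rule discards the primary outcome of ITT participants selected on a post-randomisation rating. The size is unknown and probably modest: 0.15 to 0.45 points in either direction for a 5% vs 2% split in exits and deficits of 5 to 15 points, and zero if exits and deficits are equal or there is no deficit. These rates and deficits are assumptions, and the comparison meant is between all ITT participants in their assigned arms, on or off drug.

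Confidence is medium because the full protocol may already keep visit 7; a wording correction would then be enough. The change is worth making because the loss cannot be repaired afterwards and the remedy is cheap. It is not a flaw that undermines the trial.

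**What to change.** Leave the trigger as it is, but have it discontinue study treatment instead of trial participation, with a taper. The article already defines one for the end of treatment: "the study medication will be tapered down over a period of up to 13 days".

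With consent, hold visit 7 on schedule and collect VABS-3, CGI-S and CGI-I, with the same informant and interviewer and in the baseline format where possible. Video is a workable fallback, since VABS-3 is an interview with a parent or carer and, during the pandemic, "was conducted via videoconference at the time of lockdown or whenever it was more risky for the families to attend the hospital". Analyse these participants in their assigned arm.

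The cost is a small amendment and a few more completed visits that are already scheduled: about 5 in AIMS-CT1 at 5% vs 2% exits, about 7 at 5% in both arms (rates assumed). The same change should be sought in the Canadian trial so that the pooled data stay consistent. Protection of participants is unchanged. Some families will decline, so the loss is reduced, not removed.
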